### Adverse Events

All participation in this study will be entirely voluntary, and all participants will be required to sign a written informed consent, including their rights and possible benefits and risks. Participants can refuse to participate in the study or withdraw from the study at any time during the study. If participants choose to withdraw from this study, they will not be affected, and they will not be discriminated or retaliated against.

Adverse events (AEs) can be any adverse and insignificant experimental results, symptoms, or research-related diseases [54]. Most studies have shown that Qigong treatment is a relatively safe method, with no serious AEs reported [55-57]. If AEs occur, they are defined as any damage caused by the intervention, such as headache, dizziness, chest tightness, heart palpitations, muscle aches, neurasthenia, and psychological stress. Regardless of whether it is related to treatment, the affiliated doctor of the Shanghai Municipal Hospital of Traditional Chinese Medicine will be notified on time and the AE will be recorded on the case report form. The doctor will make a corresponding judgment and start treatment. If serious AEs occur, the investigator will report those to the main investigator and the ethics committee to determine whether the participant should be withdrawn from the study and treatment. The study will be suspended for further instructions if necessary. The researchers will do their best to prevent and deal with possible damages caused by this research. If the expert committee believes that AEs are related to Qigong treatment, the research team will provide treatment costs and corresponding financial compensation for damages related to the trial.

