**Objective:**

This study aims to evaluate the efficacy and safety of the PLWNT method in terms of its effects on fatigue, insomnia, anxiety, and gastrointestinal symptoms in patients with CFS.

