### Outcome Measures

The primary outcome is the MFI-20, while secondary outcomes will include the Pittsburgh Sleep Quality Index (PSQI), Gastrointestinal Symptom Rating Scale (GSRS), Hospital Anxiety and Depression Scale (HADS), fMRI, gut microbiota, and peripheral blood. The specific study outcome assessment time points are shown in Table 1.

**Table 1 table1:** Time points of the outcomes assessment.

			Screening (T-1)^a^		Intervention								Follow up (T20)
					T0		T4	T8		T12			
Inclusion criteria			✓										
Exclusion criteria			✓										
Informed consent			✓										
Randomization					✓								

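### The adverse event section gives a causal definition that conflicts with its own broad definition and its all-cause recording rule, so the set of events behind the safety aim is ambiguous

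*Protocol article*

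**What the plan says.** Safety is part of the aim: the Objective in the Abstract is to "evaluate the efficacy and safety of the PLWNT method", and the Discussion pairs efficacy with safety again.

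The second paragraph of the Adverse Events section contains three statements on what an AE is and when it is recorded:

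- A broad definition: "Adverse events (AEs) can be any adverse and insignificant experimental results, symptoms, or research-related diseases".
- A causal definition, two sentences later, for AEs that occur: "they are defined as any damage caused by the intervention". Examples follow, among them dizziness, palpitations and aching muscles.
- A recording rule, in the next sentence: "Regardless of whether it is related to treatment", a hospital doctor is told and "the AE will be recorded on the case report form".

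Neither the causal definition nor the recording rule is limited to one arm.

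**The concern.** An AE definition decides which events exist for the safety summary. If the definition includes causation, someone must judge the cause before an event qualifies. An event judged unrelated then drops out, where it should have been recorded with its relatedness noted beside it.

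That matters more here than in a blinded drug trial. The Blinding section accepts that participants cannot be masked, and therapists know what they deliver. The judgement would therefore rest at least partly on reports from people who know the arm. The disease also makes attribution hard. Entry requires fatigue that activity makes worse, and malaise after exertion, while the experimental treatment is a daily exercise. Feeling worse after practice can be put down to the exercise or to the illness. Under the causal definition, the second choice removes the event from the AE set.

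**Working it through.** No figure in the plan bears on this point, so there is nothing to reproduce. The check sets the three statements side by side and runs example events through each. The examples are hypothetical.

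| Event | Broad definition | Causal definition | Recording rule read as all-cause |
|---|---|---|---|
| Muscle ache, PLWNT, judged due to practice | AE | AE | Recorded |
| Dizziness, PLWNT, judged due to CFS | AE (a symptom) | Not an AE | Recorded |
| Headache, CBT, judged unrelated to CBT | AE (a symptom) | Not an AE | Recorded |
| Intercurrent illness unrelated to the research | Unclear: symptoms qualify, but diseases only if research-related | Not an AE | Recorded |

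1. The statements agree only on the first row, where the event is judged to be caused by the intervention.
2. On the second and third rows the broad definition and the recording rule include the event, and the causal definition excludes it.
3. The causal definition and the recording rule cannot both have content. If every AE is caused by the intervention, there are no unrelated AEs, and the clause setting relatedness aside does nothing. If that clause does something, unrelated AEs exist and the causal definition is wrong.
4. The broad definition does not fully settle the matter, because it attaches a research link to diseases, as the fourth row shows.

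On size, let p be the true proportion of participants with an event in an arm and a the share of those events attributed to the intervention. Under the causal definition the counted proportion is about p × a. With equal p in both arms, the ratio of counted proportions is (p × a_PLWNT) / (p × a_CBT) = a_PLWNT / a_CBT. The ratio therefore equals whatever attribution shares are assumed. The documents give neither share and no p. The ratio can fall above or below 1, depending on whether symptoms after exercise are blamed on the exercise or on CFS.

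**The case against.** The strongest reply is that the working instruction is already all-cause. Setting relatedness aside makes sense only if unrelated events are recorded, and the opening definition covers symptoms without a causal condition. Staff who follow those two sentences would collect all-cause events in both arms, and the causal phrase would be a slip of wording. The Quality Control section also provides an independent steering committee with expertise in AEs and a duty to control bias. Much of this stands. It shows that the contradiction need not do harm, and it shows which way to resolve it. It does not remove the contradiction: the causal sentence is the one that says how AEs are defined, and nothing says that the other two override it.

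A reader might infer several stronger points, which the documents do not support:

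- **That the arms cannot be compared fairly on safety.** This does not follow. If the recording rule is followed as all-cause, a fair comparison is possible. The article also describes no between-arm AE test, which may be left to a fuller document.
- **That causality is assessed for Qigong only.** The sentence beginning "If the expert committee believes that AEs are related to Qigong treatment" stands at the end of the paragraph and decides treatment costs and compensation. It does not govern which events are recorded or counted.
- **That safety was left out of the outcomes.** AEs are absent from the outcome list and Table 1 but have their own Methods section. How they are tabulated may be left to the full protocol or analysis plan.
- **That AE rates will be distorted by some stated factor.** Any such factor would only restate assumed attribution shares.

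**Conclusion.** The section contradicts itself on what counts as an AE, and the set of events for the stated safety aim is ambiguous as a result. This follows from the text alone and needs no assumption.

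Bias between arms is a conditional risk. It arises only if the causal definition is applied as a filter and attribution differs by arm. The first condition is one permitted reading of the text. The second is plausible because participants and therapists are unmasked, but the documents do not establish it. Size and direction cannot be derived.

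The point is modest but should be corrected. The fault lies in a rule the article states, so it is not a matter of detail left to a longer document. An event never recorded under the causal reading would be hard to recover later.

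**What to change.** Delete the causal phrase from the Adverse Events section and put one definition in place of the two now given: an AE is any untoward medical occurrence in a participant in either arm, whatever its cause. The listed symptoms can stay as examples. This agrees with the existing recording rule, which can remain as it is.

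Record relatedness as a separate item on the case report form, worded for the assigned intervention (PLWNT or CBT) and completed in the same way in both arms. Related events can then be summarised as a subset, and a causal judgement never decides whether an event is on record.

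Recruitment began in July 2022, so it would also help to state which reading has been applied to forms already completed.

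The cost is protocol and form wording. A few more unrelated events will be recorded, so AE rates may look slightly higher than under the causal reading.

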#### PLWNT Group

The PLWNT intervention program and operating standards refer to the Chinese general higher TCM compiled from the college textbooks of Tuina and Qigong. Experienced Qigong teachers at Shanghai University of TCM, who have been teaching Qigong for at least 5 years, will be placed in charge of the supervision of the exercise, and they will correct participants’ exercise postures during the entire intervention period for 1 h every Sunday, including the first 10 min of each session for stretching and relaxation exercises, as well as movement introductions and demonstrations. The subsequent 20 min are allotted for individual guidance and correction of actions. Finally, all participants will practice PLWNT for 30 minutes together. For the remaining 6 days of the week, all participants will practice by themselves for 30 minutes at 6 PM o’clock every day at home, under the remote supervision of one of the directors. The practice videos will be required to be posted in a WeChat group comprising all of the study participants. If some participants find this inconvenient, videos can be sent privately to the study investigators. All participants will be asked to write down their feelings in a practice recording notebook after each exercise. The average amount of abdominal stimulation for the first 8 rubbings was 0.5 (SD 0.1) kg, and the strength of the stimulation will be monitored in real time in the LABVIEW2017 software (SHUTCM) so that the patients can feel the amount of stimulation. The entire practice process will last for 12 weeks. The content of the PLWNT Qigong intervention is the same as that reported in our previous research The 9 specific forms of manipulation are shown in Figure 2 [39,50].

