#### CBT Group

Qualified CBT therapists with professionally accredited qualifications will be invited to conduct CBT for 1 h each week by giving lectures or psychological consultations on the prevention and treatment of CFS. The sessions will cover CFS diagnosis, diet and nutrition, life management, health and lifestyle changes, physical and mental health education, and medical management. On the remaining 6 days of the week, all participants will be required to listen to lectures on WeChat for 30 minutes every day. If some participants find this inconvenient, they will be allowed to learn at their own pace using the PowerPoint (Microsoft Corp) presentations provided. Each participant will be asked to write down their feelings in a practice recording notebook after each web-based session to ensure that the other conditions are the same as those of the PLWNT group. The entire practice process will last for 12 weeks. Detailed information is available in a previously published paper [39,50]; however, in this research, we will focus on CBT treatment in the gastrointestinal and nervous system fields.

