### Follow-Up

After the study, the participants will resume their original life in unsupervised mode, but they will need to record daily exercise or physical activity information and send this information to the researchers by email every day. The researchers will gather the participants once a week to discuss CFS-related issues and detailed follow-up actions. They will also give gifts such as traditional Chinese medicine sachets, exercise clothing, and pain patches to thank the participants and increase their enthusiasm for follow-up. All indicators will be reassessed at 8 weeks after the end of the trial to determine the long-term efficacy.

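### Safety is an aim, but no common adverse event enquiry is described while home supervision is closer under PLWNT, so between-arm event counts may be confounded with contact

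*Protocol article*

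**What the plan says.** The Objective in the abstract is explicit: "This study aims to evaluate the efficacy and safety of the PLWNT method". The Discussion repeats safety as an aim.

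The Adverse Events section gives one route for capture. When an event occurs, whether or not it is related to treatment, a hospital doctor "will be notified on time and the AE will be recorded on the case report form". No scheduled question, checklist or interval is described. Outcome Measures says "The specific study outcome assessment time points are shown in Table 1". That table runs from eligibility checks to week 20 and has no adverse event row.

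Contact on the six home days differs by arm:

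- **PLWNT Group:** daily practice takes place "under the remote supervision of one of the directors", and practice videos are required. Quality Control has participants upload photos or videos so that the instructor receives feedback. Stimulation strength is monitored in real time, though the article does not say whether this applies at home.
- **CBT Group:** participants listen to lectures on WeChat, or, if that is inconvenient, "they will be allowed to learn at their own pace using the PowerPoint (Microsoft Corp) presentations provided". No supervision or upload is stated for this arm.

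In the 8-week Follow-Up, participants meet the researchers weekly, and "they will need to record daily exercise or physical activity information and send this information to the researchers by email every day".

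**The concern.** If events reach the case report form only when someone notices or reports them, the number recorded depends on how often and how closely participants are in contact with staff. Here that contact is described as closer in one arm on six days of each week.

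The bias could run either way. More contact could raise the PLWNT count. It could also lower it, if instructors take complaints to be a normal part of practice and do not pass them on.

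This matters for a trial whose participants must have fatigue that worsens with activity and postexertional malaise, and whose experimental arm is a physical practice. Whether PLWNT produces more complaints than CBT is a natural safety question, and raw counts would answer it poorly.

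**Working it through.** **No safety figure to reproduce.** The article gives no event rate and no detection probability. The only figure borrowed from it is 104 per arm. As a check on that figure, with difference 1.634, SD 3.238, two-sided 5% and 90% power (power is not stated in the text, so 90% is inferred):

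- n = 2 × (1.960 + 1.282)² × 3.238² / 1.634² = 82.5, rounded up to 83.
- 83 / (1 − 0.20) = 103.75, rounded up to 104. This agrees with the plan, and the point here does not depend on it.

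**Where contact is equal and where it differs**

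| Contact | PLWNT | CBT | Described as asking about events? |
|---|---|---|---|
| Weekly 1 h session | yes | yes | no |
| Six home days a week | remote supervision, videos or photos | lectures or self-paced slides | no |
| Notebook after home sessions | yes | yes | no; it records feelings, and no review for events is stated |
| Table 1 questionnaire visits | yes | yes | no |
| Weekly gatherings in follow-up | yes | yes | no |

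Home days number 6 × 12 = 72 of 72 + 12 = 84 sessions, or 72/84 = 86%, in each arm. The one row that differs therefore covers most of the 12 weeks.

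**Illustration, with all rates assumed.** Take the same true risk of 20% in both arms, 104 per arm with no loss, and PLWNT detection of 90%. Expected recorded count = 104 × 0.20 × detection. The apparent risk ratio is the ratio of the two detection probabilities. The last column is the chance of a two-sided P<.05 in a comparison of two proportions.

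| CBT detection | PLWNT count | CBT count | Apparent risk ratio | Chance of false P<.05 |
|---|---|---|---|---|
| 80% | 18.7 | 16.6 | 0.9/0.8 = 1.12 | about 6% |
| 70% | 18.7 | 14.6 | 0.9/0.7 = 1.29 | 12% |
| 50% | 18.7 | 10.4 | 0.9/0.5 = 1.80 | 38% |

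For the last row, true risks of 10% and 30% give 20% and 57%. If detection were instead lower in PLWNT by the same gaps, the risk ratios would be the reciprocals, 0.8/0.9 = 0.89 to 0.5/0.9 = 0.56. The distortion runs from negligible to large, and nothing in the article narrows it.

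**The case against.** The strongest reply is that this is a condensed article. How events are elicited, and the case report form pages themselves, are often left to the full protocol. Table 1 is a schedule of outcome assessments, so a missing row does not prove that no visit asks. Quality Control also names an independent steering committee that includes adverse event expertise and reviews the data. And the Statistical Analysis section plans no between-arm test of events. All of this stands, and it limits the point to a possible bias. It does not remove the point, because the unequal home contact is stated outright and the only stated capture route depends on notice.

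A reader might infer three stronger things that the documents do not support:

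- **That PLWNT participants are watched at every session, giving 84 observed sessions against 12, or seven-fold.** Home supervision is remote, and photos are accepted. Most of the listed events are felt and not seen, so both arms depend on self-report. The count also leaves out the notebooks, which the CBT Group section says are meant to keep conditions alike, and the shared assessments. The abstract's Methods speak loosely of treatment groups, in the plural, being supervised via web.
- **That events in weeks 13 to 20 are lost.** The Follow-Up section has researchers meet participants weekly and reassess all indicators at 8 weeks. An event question is not described there, but that is not the same as no opportunity to report.
- **That counts will reflect surveillance and not harm.** Size and direction are both unknown.

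**Conclusion.** The point holds as a possible ascertainment bias. Safety is an aim, no common event enquiry is described, and home contact is described as closer under PLWNT. Any between-arm reading of event counts may therefore be confounded with contact. With equal true risk, the apparent risk ratio would be about 1.1 to 1.8 if PLWNT detection is 90% and CBT detection is 80% down to 50%. These are assumptions, chosen only to show the range. The conclusion also assumes that the full protocol does not already schedule the same enquiry in both arms; if it does, the point falls away.

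A related matter, on which this point does not rest: the Adverse Events section says "If AEs occur, they are defined as any damage caused by the intervention", yet requires recording regardless of relatedness. Those two statements must be reconciled.

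**What to change.** At T4, T8, T12 and T20, give both arms the same short written checklist of the events named in the Adverse Events section, plus one open question, and add the matching row to Table 1. Base any between-arm safety statement on this solicited record. List spontaneously noticed events separately.

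Recruitment began in July 2022, so some visits will already have passed. For those, report solicited and spontaneous events as separate sources and do not compare raw counts between arms.

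The four assessments already exist in both arms, so the cost is a few minutes per visit and more minor events to record. If the full protocol already contains such an enquiry, one sentence in the article saying so is enough.

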### Confidentiality

To protect confidentiality, all participants will be classified by unique codes instead of names. The identity information of all participants will be kept confidential such that only the researchers will be allowed access to it. Following completion of the study, the participants’ data will be securely locked for 2 years and then destroyed under the protection of the management department. Copies of the participants’ feces and blood will be stored for 2 years with the participants’ consent.

### Quality Control

Qigong intervention plans and operating standards refer to the relevant content of the nationally compiled textbook for higher education in traditional Chinese medicine and make standard videos. Quality control will be conducted under the supervision of an independent steering committee, comprising investigators with experience in Qigong clinical trials, statistical experts, and experts in exercise and AEs, to eliminate potential bias and ensure the quality of the trial. The steering committee will be responsible for monitoring the data, identifying problems, reviewing the data collected, and controlling for bias. All instructors and evaluators must be certified to have been teaching Qigong or psychology for at least 5 years and must undergo a standardized training program conducted by a nationally recognized academic expert with at least 10 years of experience in Qigong training before the start of the trial. The training program shall be conducted in strict accordance with the PLWNT protocol, including PLWNT forms, principles, breathing techniques, concentration, and CFS precautions. Two groups will be conducted simultaneously, with a minimum of 10 people in each group, to avoid variations in the severity of CFS due to the season and weather. Participants must upload photos or videos of their home practice the remaining 6 days of the week to provide feedback to the instructor and will be encouraged via the WeChat app to complete their daily Qigong practice. The participants will not be assigned additional exercises during the study to maintain consistency in individual PLWNT strengths. At the time of enrollment, patients will undergo a 3-day training and stimulation calibration by wearing a morcellation stimulation glove. The average amount of abdominal stimulation for the first 8 rubbings will be 0.5 (SD 0.1) kg, and the strength of the stimulation will be monitored in real time using LABVIEW2017 software, so that the patients can feel the amount of stimulation. If necessary, the Qigong instructor will adjust the number and range of PLWNT movements to achieve the intended intensity.

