### Sample Size Calculation

According to our published paper, the efficacy of the PLWNT group is assumed to be better than that of the CBT group. Referring to our previously published study [47] on the efficacy of CFS with respect to the Multidimensional Fatigue Inventory 20 (MFI-20) scale, the final difference between the 2 groups in terms of MFI-20 average scores was 1.634 and the SD was 3.238. The Bonferroni conservative comparison method was used, and the sample size of this trial was calculated using the following formula:

Considering the allowable 20% dropout rate, the sample size of each group was set at 104. Therefore, this randomized controlled trial needed to recruit 208 participants.

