### Statistical Analysis

SPSS (version 25.0; SPSS Inc Chicago) will be used for statistical analysis. The baseline characteristics of patients in each group will be analyzed descriptively. All numerical data will be expressed as the average value, X̄ (SD). Quantitative data that do not fit a normal distribution will be expressed as the median (IQR). In all analyses, statistical significance will be set as a 2-tailed *P*<.05. For the primary outcome, CFS scores will be assessed using a linear mixed-effects model with time and group interaction effects. Bonferroni correction will be used to account for multiple comparisons.

For fMRI analysis, we will select the largest peak coordinate of the brain area with a difference after amplitude of low frequency fluctuations analysis, save the block where the peak coordinate is located as the mask as the region of interest, and count the difference in the functional connection density between the region of interest and the whole brain. The specific process is to make a functional connection between the seed area (amplitude of low frequency fluctuation difference brain area) and all voxels of the whole brain. Each voxel will be given a correlation value, and the normal distribution *z* scores of the 2 sets of images will be obtained using Fisher transformation, (where r is the correlation coefficient):

That is, the functional connectivity density average image. Two-sample 2-tailed *t* test will be performed between the groups, and a paired *t* test was performed within the groups. *P* values less than .05 will be taken to indicate statistical significance and the brain regions will be corrected by FWE, while XJVIEW will be used to present the results.

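### PLWNT, and at least part of CBT, is delivered in groups, but the sample size makes no allowance for clustering and the stated primary model names no class effect, so standard errors may be too small

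*Protocol article*

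**What the plan says.** Delivery: under Quality Control, "Two groups will be conducted simultaneously, with a minimum of 10 people in each group, to avoid variations in the severity of CFS", with season and weather given as the reason. Arms of 104 would meet a minimum of 10 trivially, so the natural reading is successive cohorts, each with one PLWNT group and one CBT group. The PLWNT Group section describes a weekly taught hour and adds: "Finally, all participants will practice PLWNT for 30 minutes together". The CBT Group section describes a weekly hour "by giving lectures or psychological consultations on the prevention and treatment of CFS", which leaves open how much of it is given to a group.

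Sample size: the Sample Size Calculation section takes its inputs from an earlier study: "the final difference between the 2 groups in terms of MFI-20 average scores was 1.634 and the SD was 3.238". It adds that "The Bonferroni conservative comparison method was used", without the number of comparisons, and then: "Considering the allowable 20% dropout rate, the sample size of each group was set at 104". It mentions no class size, ICC or design effect.

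Analysis: under Statistical Analysis, "CFS scores will be assessed using a linear mixed-effects model with time and group interaction effects". No class, cohort or instructor term is named.

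**The concern.** Participants are randomised individually but then treated alongside others. Where a treatment is taught and practised in a group, members of one class can come to resemble each other more than members of another class in the same arm. The group dynamic, the quality of the sessions and any adjustment the instructor makes can all contribute. Fatigue is self-reported by unblinded participants, so the primary outcome is open to such influence.

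A random effect for the participant deals with repeated measures on one person. It does not deal with correlation between classmates. If that correlation is positive and the model ignores it, the confidence interval for PLWNT versus CBT is too narrow, the false-positive rate exceeds its nominal level, and the effective sample is smaller than planned.

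**Working it through.** **Inputs from the article.** Difference 1.634; SD 3.238; 20% dropout; 104 per arm; two-sided 0.05; at least 10 per group. Standardised difference: 1.634/3.238 = 0.5046.

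**Assumed, because the article does not give them.** The ICC (0.01, 0.05, 0.10); about ten classes per arm; and the planned power with its alpha (the formula is not readable).

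**1. Reproducing the 104.** n per arm = 2(z_alpha/2 + z_beta)² / 0.5046².
- Alpha 0.05, power 90%: 2(1.960 + 1.282)²/0.2547 = 82.5, so 83.
- Alpha 0.05/3 (a Bonferroni reading), power 80%: 2(2.394 + 0.842)²/0.2547 = 82.2, so 83.
- Dropout: 83/0.8 = 103.75, so 104.

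Both readings match the stated figure exactly with a design effect of 1. Neither leaves room for clustering, and the article does not show which was used.

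**2. Clustering in both arms.** Ten classes per arm give 83/10 = 8.3 evaluable per class.
- Design effect DE = 1 + (8.3 − 1) × ICC
- Effective n = 83/DE
- Type I error if clustering is ignored = 2[1 − Φ(1.960/√DE)]
- Power = Φ(0.5046 × √(effective n/2) − z), with z = 1.960 or 2.394

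Example, ICC 0.05: DE = 1.365; effective n = 60.8; 1.960/1.168 = 1.678, so type I error is 9.3%. Then 0.5046 × √30.4 = 2.782, which gives power Φ(0.822) = 79% or Φ(0.388) = 65%.

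| ICC | DE | True SE / reported SE | Effective n per arm | Type I error (nominal 5%) | Power, alpha 0.05 (planned 90%) | Power, alpha 0.05/3 (planned 80%) |
|---|---|---|---|---|---|---|
| 0.01 | 1.07 | 1.04 | 77.4 | 5.8% | 88% | 77% |
| 0.05 | 1.37 | 1.17 | 60.8 | 9.3% | 79% | 65% |
| 0.10 | 1.73 | 1.32 | 48.0 | 13.6% | 70% | 53% |

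The power columns are for a test that uses the correct standard error. They rest on normal quantiles, so they are somewhat optimistic with this few classes.

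**3. Clustering in PLWNT only.** The variance of the comparison then inflates by (1 + DE)/2 = 1.04/1.18/1.37. Type I error is about 5.4%/7%/9.3%, and power about 89%/85%/79% on the first reading or 79%/72%/65% on the second. The inflation is about half of that in step 2.

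**4. Larger classes.** Ten is a minimum. With 10 evaluable per class in both arms, type I error at the same ICCs is 6.0%/10.4%/15.5%; with 20 it is 7.2%/16.0%/25.0%.

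**The case against.** The strongest reply is that nothing in the article shows the within-class correlation to be material. Six of the seven weekly sessions are at home. Quality Control also adds standard videos, standardised instructor training and individual calibration of the stimulation, all of which limit differences between classes. At ICC 0.01 the effect is negligible. This stands, and it makes the conclusion conditional.

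A reader might infer more than the article supports:
- *That members of a class share a chat group, an instructor and a season, all of which inflate the error.* The WeChat group comprises all participants, and no instructor is assigned to a class. Season or cohort effects common to two arms running at the same time largely cancel in the comparison. Only class effects within an arm matter.
- *That both treatments are certainly given in classes.* This is clear for PLWNT. The CBT text allows consultations, so clustering there may be partial or absent.
- *That the model definitely excludes class.* The article names a mixed model and does not list its random effects, which a fuller document could do. The sample size does not share this uncertainty: it is set in this article and reproduces without any allowance.
- *That allocation is unblocked, so cohorts could not reach 10 per arm.* The article is silent on blocking, a detail that a condensed account commonly leaves out. No criticism is made of it.

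**Conclusion.** The point holds in conditional form. Delivery is in cohorts, clearly grouped for PLWNT and probably partly so for CBT. The sample size treats participants as independent, and the model as stated names no class effect. Standard errors may therefore be too small. A reader might go further and conclude that they will be, but without an ICC the article does not support that.

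The size runs from minor at ICC 0.01 to serious at 0.10, where a nominal 5% test has a true error of about 13.6% with both arms clustered or about 9.3% with PLWNT alone. The power loss also depends on which of the two reconstructions of the 104 applies, so neither 90% nor 80% should be cited as the article's own figure. All results rest on the assumed ICCs and on 8.3 evaluable per class; larger classes make matters worse.

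**What to change.** Record the class (cohort by arm) of every participant. Add a random intercept for class to the primary mixed model, with small-sample degrees of freedom such as Satterthwaite, and include cohort as a fixed effect. If CBT proves to be individual, apply the class effect to the PLWNT arm only. If week 0 is kept as one of the modelled outcomes, let the class effect act on the post-baseline visits: an intercept common to all visits cancels from the time-by-group contrast and would correct nothing.

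Restate the power with a design effect over a range of ICCs, and give the alpha, number of comparisons and planned power that led to 104.

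The cost is one more variable, one more random term and a less favourable stated power. No extra patients are proposed. The change can be made before the data are unblinded.
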